# High-intensity interval training and energy management education, compared with moderate continuous training and progressive muscle relaxation, for improving health-related quality of life in persons with multiple sclerosis: study protocol of a randomized controlled superiority trial with six months’ follow-up

**DOI:** 10.1186/s12883-021-02084-0

**Published:** 2021-02-11

**Keywords:** Multiple sclerosis, Multidisciplinary rehabilitation, Exercise, Energy management education, High-intensity interval training, Fatigue, Quality of life, Occupational therapy, Inflammation

## Abstract

**Background:**

Persons with multiple sclerosis (PwMS) often have reduced aerobic capacity and report fatigue as the most disabling symptom impacting their health-related quality of life (HRQoL). A multidisciplinary rehabilitation approach is recommended for successful management of symptoms, although there is little supporting evidence. The aim of this study is to evaluate the effect of a multimodal therapy approach, including endurance training and patient education, during a three-week inpatient rehabilitation stay, on HRQoL in PwMS at six months follow-up. Inpatient energy management education (IEME) + high-intensity interval training (HIIT) will be compared with progressive muscle relaxation (PMR) + moderate continuous training (MCT).

**Methods:**

This study has a two-armed single-blind randomized controlled superiority trial design. One hundred six PwMS-related fatigue (relapsing-remitting or chronic progressive phenotypes; Expanded Disability Status Scale (EDSS) ≤ 6.5) will be recruited at the Valens clinic, Switzerland, and randomized into either an experimental (EG) or a control group (CG). EG: participants will perform IEME twice and HIIT three times per week during the three-week rehabilitation stay. IEME is a group-based intervention, lasting for 6.5 h over three weeks. HIIT contains of five 1.5-min high-intensive exercise bouts on a cycle ergometer at 95–100% of peak heart rate (HR_peak_), followed by active breaks of unloaded pedalling for 2 min to achieve 60% of HR_peak_. CG: participants will perform PMR twice and MCT three times per week during the three-week rehabilitation stay, representing local usual care. PMR consists of six 1-h relaxation group sessions. MCT consists of 24-min continuous cycling at 65% of HR_peak_. The primary outcome is HRQoL (Physical and Mental Component Summaries of the Medical Outcome Study 36-item Short Form Health Survey; SF-36), measured at entry to the clinic (baseline, T_0_), three weeks after T_0_ (T_1_) and at four (T_2_) and six (T_3_) months after T_0_. Secondary outcomes comprise cardiorespiratory fitness, inflammatory markers (measured at T_0_ and T_1_), fatigue, mood, self-efficacy, occupational performance, physical activity (measured at T_0_, T_1_, T_2_ and T_3_) and behaviour changes in energy management (measured at T_2_ and T_3_).

**Discussion:**

This study will provide detailed information on a multimodal therapy approach to further improve rehabilitation for PwMS.

**Trial registration:**

This trial was prospectively registered at ClinicalTrials.gov (NCT04356248; 22 April 2020).

**Supplementary Information:**

The online version contains supplementary material available at 10.1186/s12883-021-02084-0.

## Background

In persons with multiple sclerosis (PwMS), reduced aerobic capacity and impaired mobility are among the most frequent symptoms [1]. In contrast, fatigue is not easily observable, but is one of the most common [2, 3] and troubling symptoms [4], resulting in impaired health-related quality of life (HRQoL) [5] in 65% of PwMS. Living with multiple sclerosis (MS)-related fatigue affects all aspects of everyday life. PwMS increasingly delegate challenging tasks at work or in the family, and fatigue is often a major reason for them to leave or change employment, which may lead to social and financial burden [6]. On the physical and cognitive level, this vicious circle often leads to an increasingly passive lifestyle and an additional loss of physical and cognitive performance among PwMS. At the emotional level, feelings of inability and dissatisfaction and the risk of greater social withdrawal and depressive mood increase [6, 7]. The causes and consequences of MS-related fatigue are thought to be multidimensional. Guidelines and systematic reviews recommend a multidisciplinary approach, which involves exercise therapy, self-management, and education, for successful management of symptoms [8–11]. However, to date, strong evidence is available only for single unimodal interventions, such as physical therapy, training or energy management/conservation programs [12, 13].

Two systematic reviews report that educational programs and approaches based on cognitive behavioural principles reduce patient-reported fatigue [12, 14], but the relevance for patients’ functioning and HRQoL remain unclear. Recently, a three-week inpatient energy management education (IEME) program for inpatient rehabilitation was developed [15] that integrates the principles of patient education, the trans-theoretical model of behaviour change, social cognitive theory, energy conservation strategies and cognitive behavioural techniques. In a randomized controlled feasibility trial [16] IEME was compared with progressive muscle relaxation (PMR) that, in previous research, improved HRQoL in PwMS [17]. The results show that IEME has a significant effect on HRQoL and self-efficacy in performing energy conservation strategies compared with PMR at discharge. This benefit slightly increased up to four months follow-up. However, it remains unclear: (i) whether this benefit is maintained up to six months; (ii) which energy conservation strategies can be applied more frequently and more easily into the patients’ daily routine; and (iii) which barriers and facilitators IEME participants have experienced during behaviour change in energy management implementation.

Exercise programs for PwMS have been described as promising supportive therapy options for reducing symptoms and side-effects of the disease [18, 19]. However, PwMS are often inactive [20]. High-intensity interval training (HIIT) is a promising, time-saving training program for PwMS that efficiently improves aerobic capacity [21–23] and fatigue [21]. Recent intervention studies show that, in contrast to moderate continuous training (MCT), HIIT reduces indicators of inflammatory activity (serum levels of matrix metalloproteinase-2 (MMP-2) [22]) and the neutrophil-to-lymphocyte ratio (NLR) [24], associated with disability status, symptomatology and disease activity. In addition, we and others have shown that physical exercise seems to influence further biological processes, such as the kynurenine (KYN) pathway, which play a crucial role in the pathogenesis and progress of MS [22].

IEME and HIIT are both proven to be more effective than the respective standard therapies (PMR and MCT, respectively), in terms of improving HRQoL, increasing cardiorespiratory fitness and reducing indicators of inflammatory activity. The combination of HIIT and IEME, which use different therapeutic approaches (training and patient education), is recommended, but has not yet been evaluated. Therefore, this study will evaluate the effects of the combination of two different three-week inpatient therapy approaches; IEME + HIIT (experimental group; EG) versus PMR + MCT (control group; CG, representing usual care at the Valens clinic, Switzerland) on HRQoL after three weeks’ rehabilitation and after returning home (at four and six months’ follow-up) in PwMS.

We hypothesize that IEME + HIIT (EG) compared with PMR + MCT (CG) will improve HRQoL at six months’ follow-up. Secondary objectives are: (i) to evaluate the effects on fatigue and mood; (ii) to evaluate specific effects of IEME/PMR on self-efficacy in using energy conservation strategies and occupational performance; (iii) to evaluate specific effects of HIIT/MCT on cardiorespiratory fitness and disease-related biomarkers (MMP-2, KYN and NLR); and (iv) to gain additional knowledge about more frequent application of energy conservation strategies and about barriers and facilitators experienced after returning home.

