## Methods

### Design

This study is a two-armed single-blinded randomized controlled superiority trial in PwMS referred for three weeks’ inpatient rehabilitation to the Valens clinic, Switzerland. The participants’ flow is shown in Fig. 1. Outcome measures are collected at baseline (T_0_) and three weeks later, after completing rehabilitation (T_1_). Follow-up assessments are at four (T_2_) and six (T_3_) months after baseline. Before study inclusion, participants are asked to sign written informed consent.

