**Fig. 1 Fig1:**
[figure not shown]
Participant flow

Participants in the EG perform IEME on two days and HIIT on three days per week. Participants in the CG perform PMR on two and MCT on three days per week. Before the three-week intervention period, a cardiopulmonary exercise test (CPET) is performed to guide the heart rate monitored training.

CPET and blood sampling at rest are conducted at T_0_ and T_1_ to evaluate the effects of the endurance exercise modalities on fitness parameters and on specific markers in the blood suspected to be influenced by training. CPET and blood sampling are conducted 24 h before the first training session at T_0_ and 24 h after the last training session at T_1_. Patient-reported outcome measures (PROMs) are completed to evaluate short-term (T_0_ vs. T_1_) and long-term between-group effects (T_0_ versus T_2_ and T_3_) of the multimodal intervention on the HRQoL and other parameters that are relevant for a satisfying everyday life (fatigue, mood, self-efficacy in performing energy conservation strategies, self-perceived competence in activities of daily living and physical activity). After discharge, all participants receive the PROMs by post for follow-up evaluation at T_2_ and T_3_. After completion, participants return the PROMs to the research office of the Valens clinic, Switzerland. All assessments performed at T_0_ and T_1_ are conducted at the Valens clinic, Switzerland. In the EG, barriers, facilitators and maintenance of implementation of energy management strategies are evaluated using online surveys at T_2_ and T_3_.

CPET and blood sampling are performed by independent and blinded assessors. Due to the nature of this study, blinding of participants towards the allocated intervention groups is very difficult.

This study was approved by the regional ethics committee (EKOS) (EKOS20/050; Project ID: 2020–00797).

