### Randomization

Participants are randomly allocated (1:1) to either the EG (IEME + HIIT, *n* = 53) or the CG (PMR + MCT, *n* = 53). Concealed randomization is conducted by independent employees using version 1.5.2 of the Randomization in Treatment Arms software (RITA, EVIDAT, Kiel, Germany). Randomization follows the minimization procedures according to Pocock and Simon (for review see [30]). The following stratification factors are used: age, sex, MS-phenotype (relapsing-remitting, primary or secondary progressive), disease severity (EDSS score), total fatigue score of the FSMC, levels of cardiorespiratory fitness (peak wattage (Watt_peak_)) and HRQoL (EuroQol-visual analogue scales score (EQ-VAS) [31]) at baseline.

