#### Secondary outcomes

Secondary outcomes evaluate the benefits of the education interventions and endurance exercise modalities.

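### Secondary objectives ii and iii promise effects of IEME and of HIIT separately, but a two-arm package comparison cannot identify either component

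*Protocol article*

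**What the plan says.** The Background of the protocol article lists four secondary objectives. Objective ii is "to evaluate specific effects of IEME/PMR on self-efficacy in using energy conservation strategies and occupational performance". Objective iii is "to evaluate specific effects of HIIT/MCT on cardiorespiratory fitness and disease-related biomarkers", and it names three biomarkers: MMP-2, KYN and NLR.

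The Design section repeats the component-level attribution for exercise testing and blood sampling, which are done "to evaluate the effects of the endurance exercise modalities on fitness parameters" and on blood markers thought to respond to training. The same section describes the patient-reported outcomes differently. There, self-efficacy and self-perceived competence in daily activities serve to evaluate between-group effects of the combined programme.

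The structure of the trial is clear:

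- Design: "This study is a two-armed single-blinded randomized controlled superiority trial in PwMS referred for three weeks’ inpatient rehabilitation".
- Experimental group: "Participants in the EG perform IEME on two days and HIIT on three days per week".
- Control group: "Participants in the CG perform PMR on two and MCT on three days per week".
- Randomization: "Participants are randomly allocated (1:1) to either the EG (IEME + HIIT" is one arm of 53, and PMR + MCT is the other arm of 53.
- Statistical analysis: one between-subjects intervention factor with two levels, the two packages, is applied to primary and secondary outcomes.

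The article describes no arm with IEME + MCT or PMR + HIIT, no staggered start, and no assessment placed between the components.

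**The concern.** Objectives ii and iii each ask what one component does. The randomisation compares two bundles that differ in both components at once. A difference in VO2peak, MMP-2 or self-efficacy between the arms is a valid randomised estimate of the effect of the bundle. Assigning it to HIIT or to IEME is a further step that randomisation does not protect.

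What is at stake is what the trial may conclude. A biomarker or fitness difference reported under objective iii would read as randomised evidence for HIIT over MCT. A self-efficacy difference reported under objective ii would read as randomised evidence for IEME over PMR. The Discussion raises the stakes by expecting the study to inform detailed recommendations on exercise training. A fuller protocol or analysis plan could not repair this, because the limit lies in the allocation and not in the analysis.

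**Working it through.** **Inputs.** Two arms of 53 (Randomization). IEME and HIIT both given in one arm, neither in the other (Design). One two-level intervention factor (Statistical analysis). Effect size d = 0.5, α = 0.025, power 0.80, ρ = 0.65, 90 participants before dropout (Sample size calculation).

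**1. The plan's own figure.** A two-sample t-test with d = 0.5, α = 0.025 and power 0.80 needs 78 per arm, or 156 in total. The article does not state sidedness; two-sided is assumed here. The ANCOVA factor is 1 − 0.65² = 0.5775, and 156 × 0.5775 = 90.09. The stated 90 reproduces. The trial is sized for the package contrast, so what follows is not a matter of power.

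**2. The model that the objectives need.** Let I = 1 if a participant is allocated IEME (0 for PMR) and H = 1 if allocated HIIT (0 for MCT):

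E[Y] = μ + αI + βH + γ(I × H)

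Here α is the effect of IEME against PMR when MCT is given, β is the effect of HIIT against MCT when PMR is given, and γ is their interaction. Objective ii asks about α and objective iii about β.

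**3. What the arms provide.**

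- Control mean: μ
- Experimental mean: μ + α + β + γ
- Difference: Δ = α + β + γ

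This is one equation in three unknowns. If Δ were 0.5 SD, then (α, β, γ) = (0.5, 0, 0), (0, 0.5, 0), (0.25, 0.25, 0) and (0.2, 0.2, 0.1) would all fit equally well.

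**4. Check on the design matrix with 53 + 53 participants.**

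| Columns | Rank |
|---|---|
| intercept, I, H | 2 of 3 |
| intercept, I, H, I × H | 2 of 4 |
| same four columns, 2 × 2 layout (for comparison) | 4 of 4 |

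The correlation between I and H is 1.0. More participants narrow the interval for Δ but leave its split undetermined. The planned covariates do not help either, since none of them makes I differ from H. Adherence is recorded (Safety), but comparing participants by adherence to one component would be a non-randomised comparison.

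**5. Outcomes affected, counted from the objectives.**

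- Biomarkers named in objective iii: MMP-2, KYN, NLR = 3
- Fitness measures in the cardiorespiratory fitness heading: peak oxygen consumption, peak heart rate, peak wattage = 3
- Objective ii: self-efficacy, occupational performance = 2
- Total: 3 + 3 + 2 = 8

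**6. Internal consistency.** Objective ii assigns self-efficacy and occupational performance to the education component. The Design section describes self-efficacy and self-perceived competence as effects of the combined intervention, which is the quantity the trial can estimate. Nothing comparable corrects objective iii; the Design section repeats its attribution.

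**The case against.** The strongest reply is that the plan already draws its inference at package level. The Background says that the combination is under study, the hypothesis compares the packages, and no component-level test is planned. On this reading, the objectives merely name the outcomes at which each component is aimed. That choice has a stated basis: the Background and Discussion report earlier trials of IEME against PMR and of HIIT against MCT, and say that the two act on different domains of quality of life.

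Part of this stands. The planned test is the right one for the package, and the choice of outcomes is reasoned. For fitness at T1, attribution to HIIT is quite plausible, because training up to then is supervised and heart-rate-monitored in both arms. Plausibility still comes from outside the trial: the trial cannot test it, and the objectives do not present it as an assumption. It is weaker for objective ii. The Background reports that HIIT improves fatigue, and the Discussion links fitness to the energy available for daily life, so HIIT could also move self-efficacy and occupational performance.

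Three stronger readings are tempting but not supported:

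- **About 13 outcomes.** A reader might add all eight blood markers in the secondary outcome list (8 + 3 + 2 = 13). Objective iii names only three. The Design sentence does attribute blood markers to exercise in general terms, so the wider list is touched there, but the objectives themselves cover about 8.
- **The opening of Secondary outcomes repeats the error.** It reads "Secondary outcomes evaluate the benefits of the education interventions and endurance exercise modalities". This is a joint statement that assigns no outcome to one component and makes no claim that they are separable.
- **The article expects IEME to alter the exercise effect on fitness and blood markers.** The Discussion does say that energy management should help participants organise exercise, but in the setting of life after discharge. Fitness and blood markers are measured only at T0 and T1, the latter at the end of the inpatient stay.

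**Conclusion.** The point holds. Objectives ii and iii, and the Design sentence on exercise testing and blood sampling, promise something that the design cannot deliver. The component effects are fully aliased at any sample size. Two of the four secondary objectives and about 8 outcomes named in them are affected, and objective ii also conflicts with the Design section.

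The conclusion rests only on the allocation as described: two arms, both components switched together. It needs no assumption about effect size, and it does not require that an interaction exists; even with γ = 0, α and β remain inseparable. The primary hypothesis, the sample size and the planned group comparison are sound in this respect. The fault lies in the stated objectives and in the conclusions they invite.

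**What to change.** Reword three places in the protocol article:

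- **Objective ii (Background):** the effect of IEME + HIIT, compared with PMR + MCT, on education-related outcomes (self-efficacy and occupational performance).
- **Objective iii (Background):** the effect of IEME + HIIT, compared with PMR + MCT, on exercise-related outcomes (cardiorespiratory fitness, MMP-2, KYN and NLR).
- **Design, sentence on exercise testing and blood sampling:** the same package contrast in place of the effect of the exercise component.

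Add one statement: no between-arm difference will be attributed to IEME or to HIIT alone, and the matching of outcomes to components is a hypothesis that this trial does not test. The opening sentence of Secondary outcomes can stay as it is.

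The cost is a narrower claim. Conduct, sample size, data collection and analysis are unchanged. Separating the components would need a different trial, such as a 2 × 2 layout, and this point does not ask for one.

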## Methods

### Design

This study is a two-armed single-blinded randomized controlled superiority trial in PwMS referred for three weeks’ inpatient rehabilitation to the Valens clinic, Switzerland. The participants’ flow is shown in Fig. 1. Outcome measures are collected at baseline (T_0_) and three weeks later, after completing rehabilitation (T_1_). Follow-up assessments are at four (T_2_) and six (T_3_) months after baseline. Before study inclusion, participants are asked to sign written informed consent.

**Fig. 1 Fig1:**
[figure not shown]
Participant flow

Participants in the EG perform IEME on two days and HIIT on three days per week. Participants in the CG perform PMR on two and MCT on three days per week. Before the three-week intervention period, a cardiopulmonary exercise test (CPET) is performed to guide the heart rate monitored training.

CPET and blood sampling at rest are conducted at T_0_ and T_1_ to evaluate the effects of the endurance exercise modalities on fitness parameters and on specific markers in the blood suspected to be influenced by training. CPET and blood sampling are conducted 24 h before the first training session at T_0_ and 24 h after the last training session at T_1_. Patient-reported outcome measures (PROMs) are completed to evaluate short-term (T_0_ vs. T_1_) and long-term between-group effects (T_0_ versus T_2_ and T_3_) of the multimodal intervention on the HRQoL and other parameters that are relevant for a satisfying everyday life (fatigue, mood, self-efficacy in performing energy conservation strategies, self-perceived competence in activities of daily living and physical activity). After discharge, all participants receive the PROMs by post for follow-up evaluation at T_2_ and T_3_. After completion, participants return the PROMs to the research office of the Valens clinic, Switzerland. All assessments performed at T_0_ and T_1_ are conducted at the Valens clinic, Switzerland. In the EG, barriers, facilitators and maintenance of implementation of energy management strategies are evaluated using online surveys at T_2_ and T_3_.

CPET and blood sampling are performed by independent and blinded assessors. Due to the nature of this study, blinding of participants towards the allocated intervention groups is very difficult.

This study was approved by the regional ethics committee (EKOS) (EKOS20/050; Project ID: 2020–00797).

### Participants and recruitment

A total of 106 persons are consecutively recruited on the day of admission by a trained exercise scientist. The recruitment period will last 15 months. Key inclusion criteria are: age > 18 years, a definitive diagnosis of MS (revised McDonald criteria [25, 26]) with relapsing-remitting, primary or secondary progressive phenotypes, an Expanded Disability Status Scale (EDSS [26]) score ≤ 6.5, a total score on the Fatigue Scale of Motor and Cognitive function (FSMC) ≥ 43 [27], and literacy and understanding in German. Exclusion criteria are: cognitive impairment (22-point Mini-Mental State Examination score (MMSE) < 21 [28]), depression subscale of Hospital Anxiety and Depression scale (HADS) > 11 [29], women planning to become pregnant/pregnant/breastfeeding, stem cell treatment in the last six months, and participation in a previous IEME or HIIT study. All included participants undergo a brief, general medical screening for study eligibility and are excluded if they have persistent infections, cardiovascular and pulmonary diseases, or if they are unable to follow the study procedures. During the study, participants are excluded if they have acute, severe relapses or withdraw from the written consent.

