#### Primary outcome

The primary outcome of this study is the change in HRQoL over six months (T_0_ to T_3_). HRQoL is assessed using the Medical Outcome Study 36-item Short Form Health Survey (SF-36) [32]. This PROM consists of 36 items, divided into eight subscales, summarized in a Physical Component Scale (PCS) and a Mental Component Scale (MCS), with higher scores indicating better HRQoL [33]. HRQoL is assessed at T_0_ and repeated three weeks after baseline (T_1_), four months after baseline (T_2_) and six months after baseline (T_3_).

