### Sample size calculation

The a priori sample size calculation was conducted using G*Power 3.1.9.2 software [44]. It was carried out for the investigation of a between-group difference in the primary endpoint (changes in the HRQoL (PCS and MCS) from baseline to T_3_) in an analysis of covariance model (ANCOVA).

Based on our IEME feasibility randomized clinical trial [16] with four months follow-up of HRQoL, we assume a medium between-group effect size of d = 0.5 on changes in the primary endpoint HRQoL. Level of significance (α) with Bonferroni for multiple comparisons (two primary outcomes) was set at 0.025 and power (1–β) at 0.8. According to Borm et al. 2007 [45], the required sample size for the ANCOVA model was calculated with the formula (1–ρ^2^)**n*. A correlation between participant’s scores at baseline and at T_3_ of ρ = 0.65 was used. The calculation revealed that 90 participants (EG: 45 / CG: 45) would need to be recruited. Based on previous studies that apply similar interventions [16, 22], we have allowed for 18% dropout and plan to recruit 106 participants.

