### Statistical analysis

All analyses are conducted according to intention-to-treat. To determine potential effects of between-subjects factor intervention (IEME + HIIT vs. PMR + MCT) and within-subjects factor measurement time-point (T_0_ to T_3_) and their interaction on primary and secondary outcomes, 2 × 4 mixed ANCOVAs will be applied. As covariates, participants’ baseline score of each specific parameter, EDSS score, MS-phenotype, education, smoking status, occupation, time since diagnosis, age and sex will be included into the model. Post hoc Bonferroni corrected pairwise comparisons will be conducted in case of significant main effect of within-subjects factor measurement time-point. Simple effects analyses will be performed to investigate if groups differ at each measurement time-point. As effect size measures, Eta-square and Cohen’s d will be used in ANCOVA and post hoc analyses, respectively. In addition, bivariate correlation analyses will be conducted to determine potential associations between changes in HRQoL (PCS and MCS) and biomarkers/cardiorespiratory fitness/patient-reported outcomes from T_0_ to T_3_.

Statistical analyses will be performed by a statistician blinded to treatment groups, using SPSS 25® (IBM®, Armonk, NY, USA). A result will be considered significant at *p*-value ≤0.05. Because of multiple testing of the primary endpoint, alpha is adjusted in this case and a *p*-value ≤0.025 will be considered significant.

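### Excluding participants who relapse after randomisation conflicts with the stated intention-to-treat principle, and the named repeated-measures model in its usual form does not repair this

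*Protocol article*

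**What the plan says.** Three statements in the protocol article bear on who enters the primary comparison.

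- **Participants and recruitment.** After the entry criteria and the medical screening comes a rule for the period after enrolment: "During the study, participants are excluded if they have acute, severe relapses or withdraw from the written consent".
- **Statistical analysis.** "All analyses are conducted according to intention-to-treat". The model for primary and secondary outcomes is then fixed: "2 × 4 mixed ANCOVAs will be applied", with intervention as the between-subjects factor and T0 to T3 as the within-subjects factor. SPSS 25 is the software; no procedure within it is named.
- **Design.** "After discharge, all participants receive the PROMs by post for follow-up evaluation at T_2_ and T_3" (the final subscript is cut off in the quote).

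The primary endpoint is the change in the SF-36 physical and mental component scores from baseline to six months. The sample size section allows for 18% dropout.

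**The concern.** Intention-to-treat compares everyone randomised, in the arm to which they were allocated. A rule that takes people out because of something that happened after randomisation works against this, unless their outcomes are still collected and analysed.

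A severe relapse is not a neutral reason for loss. The trial enrols relapsing-remitting as well as progressive disease, and a severe relapse plausibly lowers the quality-of-life score that is the endpoint. It may also be linked to treatment. The Background argues that HIIT, unlike MCT, lowers inflammatory indicators that it calls "associated with disability status, symptomatology and disease activity". On that reasoning, relapse could differ between the arms. The two groups left after exclusion would then no longer be comparable by randomisation, and the result would still carry the intention-to-treat label.

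The choice of model can add to this. A mixed ANCOVA run as a classical repeated-measures analysis discards anyone who lacks one of the four time-points. Someone who returns the six-month questionnaire but not the four-month one would drop out of the six-month comparison as well.

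**Working it through.** **1. Side by side.** The relapse rule follows the entry and screening exclusions and is expressly about the time during the study, so it reaches past randomisation. *Excluded* can mean three things:

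| Meaning | T3 outcome collected? | In the analysis? | Compatible with intention-to-treat? |
|---|---|---|---|
| Study intervention stops | yes | yes | yes |
| Follow-up ends | no | T3 value lost | no |
| Removed from analysis | perhaps | no | no |

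The article does not say which is meant. Two of the three conflict with the analysis section.

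**2. The plan's own sample size.** Inputs from the Sample size calculation section: d = 0.5, α = 0.025, power 0.80, ρ = 0.65. A two-sided, two-sample t-test (noncentral t) needs 78 per arm, 156 in total. The ANCOVA factor is 1 − 0.65² = 0.5775, and 156 × 0.5775 = 90.1. The stated 90 is reproduced. The stated 106 corresponds to 90 × 1.18 = 106.2.

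**3. Power by number analysed.** The residual SD is √0.5775 = 0.760, so the standardised difference is 0.5/0.760 = 0.658. With n per arm the noncentrality is 0.658 × √(n/2), on 2n − 3 degrees of freedom, at two-sided α = 0.025.

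| Analysed | Derivation | Power |
|---|---|---|
| 106 | everyone contributes T3 | 0.865 |
| 90 | the plan's target | 0.798 |
| about 87 | 106 × 0.82 = 86.9 | 0.783 |

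**4. Extra loss if only complete cases count.** The documents give no rate of intermittent missingness. Assume that, among those who return T3, a share m misses T1 and independently a share m misses T2. The number analysed is then 86.9 × (1 − m)².

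| m (assumed) | Analysed | Power |
|---|---|---|
| 3% | 81.8 | 0.754 |
| 5% | 78.4 | 0.734 |
| 10% | 70.4 | 0.680 |

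T1 is assessed in the clinic, so the lower values of m are the more plausible for that visit.

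**5. Bias from leaving out relapsing participants.** Let r be the proportion relapsing and e the loss in outcome from a relapse, in SD, for the experimental (E) and control (C) arms. Assume that relapsing participants would otherwise have scored like the rest of their arm. If D is the difference among those who do not relapse, the difference among all randomised is D − (rE·eE − rC·eC). The exclusion estimate is therefore off by rE·eE − rC·eC. With the same e in both arms this is e × (rE − rC).

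- Difference of 5 points, e = 0.5: 0.05 × 0.5 = 0.025 SD
- Difference of 10 points, e = 1.0: 0.10 × 1.0 = 0.10 SD

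That is 5% to 20% of d = 0.5. The documents give neither r nor e. If relapses are fewer in the experimental arm, exclusion understates the benefit; if they are more frequent there, it overstates it. With equal rates and equal effects it is zero.

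**The case against.** The strongest reply is that the only sentence on the analysis population says intention-to-treat, whereas the relapse rule stands in the recruitment section and does not mention analysis. The Design section has the questionnaires posted to all participants. One can read the rule as ending the study intervention only. That reading is possible, and for that reason the text does not show that relapsing participants' data are discarded. It is not the only reading, and nothing in the article selects it.

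Secondly, the article names no SPSS procedure, and rules for missing data are commonly left to a full protocol or analysis plan that is not shown. Imputation before the ANCOVA would be compatible with the text. This stands. Deletion of incomplete cases is how such a model usually behaves, not something the article states. A reader might conclude that the trial will report a completer analysis under an intention-to-treat label; the documents support that only as a likely consequence of the wording.

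Thirdly, the size may be small. The rates and effects above are assumed. If HIIT lowered relapse, exclusion would hide benefit, which is conservative for a superiority claim. The Background links HIIT to markers and the markers to disease activity; it does not say that HIIT changes relapse rates. All of this is fair, and it limits the bias argument to a possibility of unknown sign.

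Two further inferences should be resisted. Withdrawal of consent stands in the same sentence, but it unavoidably ends data collection and does not contradict intention-to-treat. Stacking an assumed 10% relapse loss on the 18% (106 × 0.72 = about 76 analysed, power about 0.72) is not supported, because the 18% allowance may already include relapse exclusions.

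**Conclusion.** The point holds in a limited form. The relapse rule and the intention-to-treat statement are in conflict as written. This is a stated rule that is fixed badly, not a detail left to another document. Under two of the three meanings of exclusion, six-month outcomes are lost selectively.

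The bias has unknown size and direction: 0.025 to 0.10 SD under the assumptions shown, and zero if relapse rates and effects are equal in the arms. On precision, under the plan's own assumptions an 18% loss alone leaves about 87 participants and power of about 0.78, against 0.865 if all 106 contributed. The gap between these figures comes from all causes of dropout; how much of it is due to the relapse rule cannot be determined. The point about the model is conditional on the ANCOVA being run in its usual repeated-measures form.

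The main reason to act is that the population analysed might not match its label, and outcomes that are never collected cannot be recovered afterwards.

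**What to change.** 1. Reconcile the two sections. State that relapse is not a reason to end outcome follow-up or to leave the analysis. Keep posting the T2 and T3 questionnaires to all randomised participants who have not withdrawn consent, and analyse them as allocated. Whether training continues after a relapse is a clinical matter and is not judged here.
2. Replace the 2 × 4 mixed ANCOVA by a likelihood-based mixed model for repeated measures, with T1 to T3 as outcomes and T0 as covariate. Every observed post-baseline visit then counts, and the T3 contrast remains the primary test. The model relies on missingness being explained by the observed data, and it does not restore the 0.865 power when T3 values are missing.
3. Run the analysis without relapsing participants only as a sensitivity analysis, labelled as such.

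The cost is revised wording, a few more postal questionnaires and some added variance from scores after a relapse. The recruitment target need not change for this.
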